There is also a relative paucity of data on long-term outcomes; quality of life, urinary, bowel and sexual function in randomized controlled trials comparing surgical approaches to hysterectomy for which well-validated instruments on pelvic organ function would need to be applied in a standardised manner [2]. In addition, postoperative recovery and quality of life should be regarded as key outcomes in trials on approaches to hysterectomy for benign disease as these are the ultimate tests of effectiveness. To date there is no study which has considered quality of life, pelvic organ function and cost-effectiveness for the three main types of hysterectomy. The aim of this study is to provide evidence on the optimal type of hysterectomy in terms of cost-effectiveness by way of a three-armed randomized controlled trial (RCT) between NDVH, TLH and TAH in a low-resource setting.

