### Objectives

We hypothesize that TLH and NDVH are better than TAH in terms of time to recover, quality-adjusted life years (QALYs), pelvic organ function and cost-effectiveness. It will have the added advantage of providing valuable information on health-related quality of life, pelvic organ function and costing for the commonest gynaecological major surgical procedure.

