#### Primary objectives

To find out the time to recover after surgery following TLH, NDVH and TAH.To calculate the total cost per surgery from a societal perspective for TLH, NDVH and TAH.To compare the cost-effectiveness of TLH versus NDVH versus TAH.

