### Sample size calculation

The primary outcome is the time to recover following surgery. A difference of 7 days was considered a clinically significant difference based on time to recover following TAH (28.1 days, SD 9.5), VH (21.3 days, SD 8.5) and LAVH (19.7 days, SD 7.5 days) in a study published in the *BJOG* by Ottosen et al. [7]. Using the mean and SD of the above data, a type 1 error of 0.01 and a power of 80% with a loss to follow-up of 20% produces a sample size of 49 patients per arm (total of 147). The reason for a type 1 error of 0.01 (two-sided) was for a Bonferroni adjustment for multiplicity to keep the overall *p* value to less than 0.05 after pairwise comparisons.

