### Economic evaluation

The economic evaluation will take societal perspective and will include direct costs related to utilization of healthcare resources in the hospital and indirect costs which are borne by the patient. A micro-costing approach will be adopted to calculate utilization of hospital resources from the time of presentation to the gynaecology clinic up to six months after surgery. Incremental cost-effectiveness ratios (ICER) will be obtained by calculating the incremental costs divided by the incremental effects (time to recover and QALYs gained) for the intervention groups (NDVH and TLH) over the standard care (TAH) group.

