There is very limited information on costs related to healthcare interventions in Sri Lanka possibly due to a misconception of *‘free health’*. The societal viewpoint in calculating costs in our study will generate an accurate picture of both direct hospital-related and indirect patient-related costs. The micro-costing approach used in this study is reported to be the most accurate method in calculating hospital cost [25]. Therefore, this study will provide valuable information on costing a surgical intervention, the methodology of which will be helpful across the board for other specialities as well as similar scenarios in other developing countries.

Sri Lanka is a lower-middle-income country, and as such it is important for us to enquire in to cost to ensure that maximum value for money is obtained with the limited resources at hand. Therefore, cost-effectiveness should be the benchmark to assess healthcare interventions in such a backdrop. This study will shed light on the optimum type of hysterectomy in terms of cost-effectiveness considering both the clinicians and patients’ perspectives.

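### The primary economic objective compares three routes, but the only ICERs defined are NDVH over TAH and TLH over TAH, and these two ratios do not order TLH against NDVH

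*Protocol article*

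**What the plan says.** Three places in the protocol article set a three-way question. The Primary objectives include "To compare the cost-effectiveness of TLH versus NDVH versus TAH". The Background gives the aim as to "provide evidence on the optimal type of hysterectomy in terms of cost-effectiveness". The Discussion promises that "This study will shed light on the optimum type of hysterectomy in terms of cost-effectiveness".

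The Economic evaluation section, repeated in the Abstract, then fixes the analysis. The ICER is "incremental costs divided by the incremental effects (time to recover and QALYs gained"), and it is calculated "for the intervention groups (NDVH and TLH) over the standard care (TAH) group". No other increment is defined: there is no TLH versus NDVH ratio, no ordering by cost and no dominance step.

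The Data analysis section compares time to recover between all pairs by Cox regression, and cost across the arms by Kruskal-Wallis with post hoc comparisons. It defers further detail to a Statistical Analysis Plan, which is not shown.

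**The concern.** The three routes are mutually exclusive choices for the same woman. To choose among them, one needs each route's extra cost and extra effect over the next less costly route that is still in contention. Two ratios against a common comparator answer a different question: whether each new route is good value if the only alternative is TAH.

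The difference matters when most of TLH's gain over TAH is already available from NDVH. TLH's cost per day saved, averaged over its whole gain from TAH, can then look modest while the additional days beyond NDVH are expensive. It also matters if the trial's hypothesis succeeds. If both new routes are cheaper and better than TAH, the remaining question is TLH against NDVH, and no ratio is planned for it.

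**Working it through.** **The plan's own figures.** The documents contain no cost and no ICER to reproduce. The stated sample size does reproduce. With pooled SD √((9.5² + 8.5²)/2) = 9.01, a 7-day difference, two-sided α of 0.01 and 80% power, n = 2 × (2.576 + 0.842)² × 9.01² / 7² = 38.7, so 39. Then 39/0.8 = 48.75, so 49 per arm. This is not in dispute; the 39 is used below.

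**Inputs.** The Sample size calculation gives mean recovery times for "TAH (28.1 days, SD 9.5), VH (21.3 days, SD 8.5) and LAVH (19.7 days, SD 7.5 days"). VH is taken for NDVH and LAVH for TLH.

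- TLH over TAH: 28.1 − 19.7 = 8.4 days saved
- NDVH over TAH: 28.1 − 21.3 = 6.8 days saved
- TLH over NDVH: 21.3 − 19.7 = 1.6 days saved

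**Formula.** Let TLH cost C more than TAH (C > 0, assumed), and let NDVH cost k × C more than TAH.

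- Planned ratio, TLH over TAH: C / 8.4
- TLH over NDVH: (1 − k) × C / 1.6
- Second divided by first: (1 − k) × 8.4/1.6 = 5.25 × (1 − k)

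| NDVH excess as share of TLH excess (k, assumed) | TLH-over-NDVH ratio as a multiple of TLH-over-TAH ratio |
|---|---|
| −0.25 | 6.6 |
| 0 | 5.25 |
| 0.5 | 2.6 |
| 6.8/8.4 = 0.81 | 1.0 |
| 100/120 = 0.83 | 0.875 |

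**In assumed cost units above TAH.**

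- NDVH +100, TLH +200: the planned ratios are 100/6.8 = 14.7 and 200/8.4 = 23.8 per day; TLH over NDVH is 100/1.6 = 62.5. For a willingness to pay between 23.8 and 62.5, TLH is good value against TAH, yet NDVH has the higher net benefit.
- NDVH +100, TLH +120: the planned ratios are 14.7 and 14.3; TLH over NDVH is 20/1.6 = 12.5. NDVH is now extendedly dominated and drops out, so TLH's ratio against TAH is the relevant one and nothing misleads.

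**Both new routes dominate TAH.** Each planned ratio is then a saving divided by a gain, hence negative. A negative ratio becomes larger in size with a bigger saving but also with a smaller gain, so its size gives no ordering.

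**Precision of the divisor.** With SDs of 8.5 and 7.5 and 39 evaluable per arm, the standard error of the TLH − NDVH difference is √((8.5² + 7.5²)/39) = 1.8 days. The 95% interval is about 1.6 ± 3.6, or −2.0 to 5.2 days, so the multiples above are not stable quantities.

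**The case against.** The strongest reply is that nothing is lost. Both ICERs need incremental cost and effect against the same TAH arm, and subtracting one pair from the other gives TLH minus NDVH. Total cost per surgery for each route is itself a primary objective, and recovery is compared between all pairs. Net benefit against a common comparator also ranks three options correctly. This stands as far as the data go: the increment can be calculated. But the stated analysis is the ratio, and ratios alone do not carry the increments. The separate tests do not fill the gap, since a hazard ratio and a rank test give neither a difference in mean cost nor one in mean days, and neither combines cost with effect. Subtracting reported increments also gives no joint uncertainty, because both share the TAH arm.

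Second, TAH is the control and standard care, and the hypothesis is framed against it: "We hypothesize that TLH and NDVH are better than TAH in terms of time to recover". That explains the comparator, and the ratios answer that question directly. They remain incomplete for the three-way objective.

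Third, frontier and dominance detail often belongs in an analysis plan, and one is promised. That is fair for presentation. The comparator, however, is stated positively in two places and does not match a primary objective, so a plan that follows this text inherits the gap.

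A reader might infer more: that the trial cannot answer its economic question, or that it will declare TLH cost-effective when NDVH is better. The documents do not support either. Cost and effect are collected in all arms, no threshold or rule for choosing a route is stated, and the costs that decide the direction are not given.

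**Conclusion.** The point holds as a mismatch between a stated analysis and a primary objective. Taken as ratios, the two ICERs against TAH leave the TLH versus NDVH choice open, do not reveal dominance between the new routes, and cannot be ranked if both dominate TAH.

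The size is illustrative only. It assumes that TLH costs more than TAH and that LAVH recovery stands in for TLH, and it covers recovery days, not QALYs. On that basis the planned TLH ratio understates the TLH-over-NDVH ratio when NDVH's excess cost is below about 81% of TLH's, and overstates it above that. A misleading reading is therefore possible but not certain. The Background reports high direct costs for TLH, evidence that VH costs less than LH, and lower indirect costs that may favour TLH over TAH, so neither the understating case nor the case where both routes dominate TAH is far-fetched.

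**What to change.** Replace the ICER sentence in Economic evaluation and its copy in the Abstract, and carry the change into the Statistical Analysis Plan before the database is opened. For each effect measure:

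- rank the three routes by mean cost;
- remove dominated and extendedly dominated routes;
- calculate each ICER against the next less costly remaining route, including TLH versus NDVH where both remain, or report net benefit for all three;
- show joint uncertainty across the three routes, for example the probability that each is optimal over a range of willingness to pay;
- keep the ratios against TAH as secondary, since they answer the hypothesis as framed.

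The cost is a short change of text and a small extra analysis. Design, sample size and data collection are unaffected.

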### Resource use and costs

Direct costs would include surgical costs, clinic costs, investigation costs and care during hospital stay. Surgical costs will consider staff cost, equipment cost, anaesthetic costs and cost of basic utilities; water, electricity and building cost. Clinic costs will entail staff cost, equipment cost and cost of basic utilities for clinics during the preoperative and postoperative period. Investigation costs will include laboratory and imaging costs for preoperative period and postoperative period. Information on routine investigations; full blood count, blood urea, serum electrolytes, urine full report, ECG, chest X-ray, transvaginal ultrasound scan (TVS) and any other additional investigation would be collected from clinic and in-ward medical records by the data collector on to a data sheet. The cost of hospital stay will include staff costs, cost of medicines and basic utilities. Information on healthcare costs were obtained from the medical supplies division of the Ministry of Health, Sri Lanka. Information on labour costs and basic utilities were obtained separately for each centre. Indirect costs will consider costs of additional investigations and medicines paid for by the patient, travel costs to and from the hospital/clinic, cost for carers and productivity losses for the patients and families and will be obtained by patient-filled questionnaires.

### Organisational structure

The study office is in the professorial obstetrics and gynaecology unit of the faculty of medicine, University of Kelaniya. It communicates with North Colombo Teaching Hospital-Ragama and District General Hospital, Mannar on specific issues. Each site is responsible for randomization and data collection. Monthly meetings are held in the study office with the participation of the involved gynaecologists at North Colombo Teaching Hospital, Ragama and the lead gynaecologist from District General Hospital, Mannar to ensure the smooth running of the trial. Six monthly updates will be provided to the Faculty of Graduate Studies of the University of Kelaniya and the Sri Lanka Clinical Trials Registry (SLCTR) along with yearly progress reports to the funding agency, National Research Council (NRC) of Sri Lanka. The study is supervised by its project management group, which consists of a representative of the grant agency and representatives from the study centres.

### Local organisation in centres

Each centre will have a lead gynaecologist who will be the point of contact for that centre whose responsibilities will be: to establish the study locally, obtaining the required regulatory approval; to appoint and train a local research assistant; to inform all relevant local staff about the study (e.g. other consultant gynaecologists, junior medical staff, research assistants and ward staff); take responsibility for complications of the study locally; and notify the study centre of any unexpected complications due to the study. Fortnightly meetings involving gynaecologists, research assistants, junior medical staff and paramedical staff will be held at each local centre. The involved gynaecologists will identify eligible patients, explain the different surgery options to them, and ensure that study documentation has been provided and that informed consent has been obtained.

Each centre will have a local research assistant to organise recruitment of patients to the study. The responsibilities of the research assistant will be to: ensure that each participating patient has received the patient information leaflet and has given informed written consent, ensure that each participant has received all self-administered questionnaires, collect all relevant medical data on to the data sheet, keep a log of all eligible women and their recruitment status, maintain a register of all recruited patients, contact participants at relevant assessment points to obtain required data (at 1 week, 6 weeks, 3 months, 6 months and 1 year), systematic filing of study documents, data entry on to the computer database, notify the local lead gynaecologist of any problem or complication and inform local staff of progress of the study. In order to improve recruitment, research assistants will identify any eligible women in the ward who may have been missed at the gynaecology clinic.

### Research governance

The computer unit of the Faculty of Medicine, University of Kelaniya will help to provide centralised database support. The principal investigator will ensure that sufficient mechanisms are in place for monitoring the quality of the study with timely routine reports of adverse effects. The trial will comply with the UK Data Protection Act 1998. The trial statistician will have access to the final trial dataset and will manage access rights to the dataset. If compliance with legal, data protection and ethical guidelines are met anonymised trial data will be shared with other researchers once all planned data analysis is complete.

### Safety monitoring and premature termination of study

All surgeries will be done by consultants competent in the relevant type of hysterectomy, i.e., for an example all hysterectomies will be done by specialists who have operated on a minimum of 25 procedures. Any complication would be managed as per standard guidelines and necessary multidisciplinary input sought if required. All complications will be reviewed by an independent clinical review panel comprising three experienced gynaecologists. A list of all the possible complications will be made available at each site. It is the responsibility of the researchers and all other grades of staff to inform the clinical review committee of any complication through incident report forms, which are available in each setting. The clinical review panel will assess if the complications in the TLH or NDVH group exceed in amount or severity compared to the standard treatment (TAH group). If so, the disadvantaged arm of the study will be terminated.

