### Outcome measures

The primary outcome is time to recover following hysterectomy (earliest time to resume all or a combination of activities done prior to surgery; resumption of cooking, washing clothes, sexual activity and occupation). The secondary outcomes are operative time (skin to skin), postoperative hospital stay, anaesthesia time, complications (bladder injury, ureteric injury, bowel injury, convert to laparotomy, vault haematoma, blood transfusion, postoperative fever, skin wound infection, urinary tract infection, respiratory tract infection, deep vein thrombosis/pulmonary embolism, re-operation), postoperative pain and total pain medication per day per patient, QALYs, urinary, sexual and bowel function and total cost per surgery. The outcome measures are shown in Table 1.

**Table 1 Tab1:** Outcome measures and study instruments

Outcomes	Study instrument
Time to recover	Patient filled data sheet at 6 weeks
Operative time	Data sheet on operative period filled by research assistant.
Postoperative hospital stay	Postoperative data sheet filled by research assistant
Cost	Direct costs based on preoperative, operative, postoperative, 6-week and 6-month data sheets filled by research assistant Indirect costs based on preoperative, postoperative, 6-week and 6-month data sheets filled by patient
Complications	Data sheet on operative, postoperative, 6-weeks and 6-months period filled by research assistant
Anaesthesia time	Data sheet on operative period filled by research assistant
Pain scores and pain medication	Data sheet on postoperative period filled by research assistant
Blood loss/change in haematocrit	Data sheet on operative and postoperative period filled by research assistant
QALYs	Paper-based EQ-5D-3L (Sinhala/Tamil) [16]
Urinary function	ICIQ-FLUTS (Sinhala/Tamil) questionnaire [18, 19]
Vaginal and sexual function	ICIQ-VS (Sinhala/Tamil) questionnaire [20]
Bowel function	Bowel symptoms questionnaire [21]

*EQ-5D-3L* EuroQoL group questionnaire on health-related quality of life, *ICIQ-FLUTS* International Consultation on Incontinence modular Questionnaire on Female Lower Urinary Tract Symptoms, *ICIQ-VS* International Consultation on Incontinence modular Questionnaire on Vaginal Symptoms, *QALYs* Quality-adjusted life years

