### Randomization

Block randomization in multiples of three will be carried out at each study site by opening sealed envelopes containing computer-generated block randomization numbers, with block sizes of six and nine to ensure roughly equal numbers of patients in each arm at any point in the study. The patients and medical team will not be blinded to the intervention with only the statistician performing the analyses being blinded.

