### Patient selection and data collection

Eligible patients will be identified, counselled and enrolled by gynaecologists at each study centre. Before entry into the study the gynaecologist will explain to a potential patient the aims, methods, reasonably anticipated benefits and potential hazards of the study. Patient information sheets will be distributed to eligible patients and a research assistant will be available for a more detailed explanation. They will also explain to patients the potential benefit of extended long-term follow-up that would otherwise not be available and other intended benefits to the healthcare system as well as the country by participation in this research. After sufficient information, informed written consent will be obtained. Research assistants will assign enrolled participants to have either a TLH, NDVH or a TAH (Fig. 1). Patients who decline participation in the study will have standard treatment (TAH).

A preoperative questionnaire on general information, quality of life, pelvic organ function (urinary, vaginal and sexual and bowel function) and costs incurred up to surgery would be filled in by the patient while another on relevant medical information would be filled by a research assistant a day prior to surgery. Standard techniques of TLH, TAH and NDVH would be followed [15, 16]. The decision to convert to laparotomy at TLH or NDVH would be at the discretion of the primary surgeon.

Data on operative time, complications, instruments and medications used and staff allocation during surgery will be entered into a data collection sheet immediately after surgery. During the postoperative period the following information will be collected by a research assistant using a datasheet; complications, pain scores and analgesic medication and investigations. A patient-filled questionnaire will obtain costs incurred by the patient due to hospital admission. The health utility scores based on paper-based EuroQoL group health-related quality of life (EQ-5D-3L) questionnaires will be estimated on day 2 and 1 week post-surgery. (A self-addressed stamped envelope along with an EQ-5D-3L form will be provided to the patient on discharge with instructions to mail the 1-week assessment).

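### The panel that can close an arm is stated to receive complications only through incident forms from unblinded staff, with no stated check against the complication sheets kept for every woman

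*Protocol article*

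**What the plan says.** **Route to the panel.** Under Safety monitoring and premature termination of study, an independent panel of three gynaecologists is to review all complications. The duty to report falls on researchers and on staff of every grade, and the channel is fixed: "to inform the clinical review committee of any complication through incident report forms, which are available in each setting". A list of possible complications is held at each site. The panel judges whether complications in TLH or NDVH exceed those in TAH in amount or severity. If they do, the disadvantaged arm is terminated.

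**Blinding.** The Randomization section states: "The patients and medical team will not be blinded to the intervention with only the statistician performing the analyses being blinded".

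**The other record of complications.** Complications are also a secondary outcome. Table 1 gives their instrument as "Data sheet on operative, postoperative, 6-weeks and 6-months period filled by research assistant". The section on patient selection and data collection says that operative data, complications included, "will be entered into a data collection sheet immediately after surgery", and it assigns postoperative capture to the research assistant: "During the postoperative period the following information will be collected by a research assistant using a datasheet; complications".

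**A further notice.** Under Local organisation in centres, the lead gynaecologist must "notify the study centre of any unexpected complications due to the study". The research assistant must tell that lead of any problem or complication.

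**The concern.** A comparison that can close an arm needs complications to be ascertained equally in all arms. An incident form exists only when someone raises it, so a woman without a form may have had no complication or an unreported one. The sheets are designed to be completed for every woman and can separate the two. As written, an irreversible decision rests on the less systematic of two sources, and no link between them is stated.

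The people raising forms know the arm. TAH is the standard treatment, and the panel's question is posed only as an excess in the other two arms. Staff might report more readily in the arms under scrutiny, which would make a harmless arm look worse. They might instead report less readily there, which would conceal real harm. The first error could cost the trial an arm without cause; the second is a patient-safety failure.

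**Working it through.** **1. The two records side by side.**

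| | Incident forms | Complication sheets |
|---|---|---|
| Trigger | An event that someone reports | Fixed periods: operative, postoperative, 6 weeks, 6 months |
| Completed by | Researchers and all grades of staff | Research assistant |
| Separates no event from no report | No | Yes, if completed |
| Stated to reach the panel | Yes | No |
| Blinded to arm | No (medical team) | Not stated; research assistants assign the arms |

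**2. The denominator.** The plan has 49 women per arm. With a 7-day difference, SD = √((9.5² + 8.5²)/2) = 9.014, two-sided α of 0.01 and 80% power, the normal approximation gives 39 per arm. Allowing for 20% loss, 39/0.8 = 48.75, rounded up to 49. The plan's figure is reproduced. It is used below only as the arm size.

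**3. Effect of unequal reporting.** The article gives no complication risk and no reporting rate, so both are assumptions. Let the true risk be p in every arm and the reported share r. Reported counts are then Binomial(49, p·r), independent between arms.

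For any excess in at least one newer arm, where X is the TAH count and F the cumulative distribution in TLH or NDVH:

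P = Σₓ P(X = x)·[1 − F(x)²]

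For a stricter reading, the same sum counts only excesses with two-sided Fisher p<0.05 against TAH. Reporting in TLH and NDVH is fixed at 90%.

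| True risk | TAH reporting | Expected reports, each newer arm v TAH | Any excess | Fisher p<0.05 |
|---|---|---|---|---|
| 20% | 90% | 8.8 v 8.8 | 61% | 2.4% |
| 20% | 70% | 8.8 v 6.9 | 81% | 7.6% |
| 20% | 50% | 8.8 v 4.9 | 94% | 20.7% |
| 10% | 90% | 4.4 v 4.4 | 60% | 1.5% |
| 10% | 70% | 4.4 v 3.4 | 74% | 3.4% |
| 10% | 50% | 4.4 v 2.5 | 87% | 7.4% |

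Expected reports are 49·p·r; for example, 49 × 0.20 × 0.70 = 6.9.

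**4. The opposite direction.** With 60% reporting in the newer arms and 90% in TAH, the chance of any excess falls to 26% at 20% risk and 34% at 10% risk, although the true risks are equal. Under-reporting of this kind would similarly mask a real excess.

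**5. What the table isolates.** The effect of ascertainment is the change from the first row within each risk: at 20% risk, 81 − 61 = 20 percentage points for any excess, and 7.6 − 2.4 = 5.2 under the Fisher criterion. The 61% itself arises with equal reporting. It belongs to the separate problem that a bare excess is often met by chance.

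**The case against.** **The duty to report is universal.** Every grade of staff must report every complication, a common list is held at each site, and all complications are to be reviewed. The research assistant must also escalate any complication to the local lead. The article further mentions regular data checks at both centres and routine reports of adverse effects, without naming who receives the latter. All this stands, and it makes selective reporting less likely. None of it says that forms are reconciled with sheets before the panel compares the arms.

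**The local-lead notice is not an input to the panel.** A reader might infer that the filter on unexpected, study-related complications shapes what the panel sees, so that TAH events would be under-reported. The article does not support this. That notice goes to the study centre, and the panel's stated criterion is any complication. The two wordings differ and should be reconciled, but the difference fixes no direction of bias.

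**Denominators exist.** Each site keeps a register of recruited women, and blocks of six and nine keep the arms roughly equal. This is correct; the weakness is incomplete or unequal numerators.

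**The figures are hypothetical.** The reporting rates are assumed, and the high percentages depend on reading a one-event excess as enough to end an arm. This also stands, and it is why the Fisher column is shown beside them.

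**A full protocol or panel charter might add the cross-check.** It might. The point concerns what the article does state: it specifies the route to the panel, and that route is the forms.

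**Conclusion.** The point holds as a weakness in the stated method, not as a demonstrated bias. The only stated route to a panel with power to end an arm is event-triggered reporting by people who know the allocation, while a more systematic record of the same events is already being collected. Reporting that differs by arm could exaggerate or conceal an excess.

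Its size depends on assumptions that the article cannot settle. With equal true risk of 20% and reporting of 90% against 70%, the chance of an apparent excess in TLH or NDVH rises from 61% to 81% on the most literal reading of the rule, and from 2.4% to 7.6% under a conventional significance criterion. A reader might take the 81% or 94% as the chance that this trial wrongly loses an arm. It is not: those values combine invented reporting rates with the separate absence of a threshold. The change is worth making because it is cheap and removes the dependence on who chooses to report.

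**What to change.** - **Safety monitoring section:** state that the panel's between-arm comparison uses periodic tabulations from the per-woman complication sheets (operative, postoperative, 6-week and 6-month, as available). For each arm, give the number of women with each listed complication, and its severity, over the number operated on. Severity must stay in, because the panel's remit covers both amount and severity.
- **Incident forms:** keep them as rapid alerts, and reconcile them against the sheets before each tabulation.
- **Local organisation in centres:** reconcile the notice limited to unexpected, study-related complications with the duty to report any complication in the Safety monitoring section.

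The cost is protocol wording and a recurring table from data already collected. There are two drawbacks. Tabulations reach the panel slightly later than forms, which is why the forms stay as alerts. The research assistants are not said to be blinded, so the sheets equalise the opportunity to record an event without blinding its assessment.
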